**Fig. 3 Fig3:**
[figure not shown]
Derivation of reference standard flow chart

### Histopathological data processing and collection

The clinically most appropriate biopsy route for each patient will be used to obtain tissue, as informed by the mp-MRI and discussed and documented at the prostate Multi-disciplinary Team (MDT). Decision to biopsy or perform prostatectomy will be based on mp-MRI (not VERDICT MRI).

Tissue samples will be collected, fixed in formalin and embedded in paraffin. Sections will be and stained with hematoxylin and eosin (H&E) as per standard national health service (NHS) protocols. Immunohistochemical staining will also be performed for blood vessels and capillaries as per standard methods.

Histopathological assessment will be performed by two blinded histopathologists independently and then in consensus. Biopsy and whole block sections taken will be analysed after conventional H&E staining to assess tumor morphology including Gleason score, tumor volume/cancer core length, cell density, cell size distribution and percentage of epithelium/stroma. In addition immunohistochemistry for vascular markers will be performed for assessment of microvessel density.

To quantify the prostatic tissue components, automated segmentation of the core biopsies shall be performed, mapping blood vessels, lumen, epithelial cells and stroma using software developed in house.

In addition, detailed histological correlation will be sought for each of the specific imaging findings. A database table will be constructed listing the imaging observations and the histological findings listed in Table 4, with histological scores provided for each main observation.

**Table 4 Tab4:** Imaging parameters vs. histological correlates

VERDICT parameter	Histological parameter
Intracellular volume fraction	Cell coverage fraction per high power field
Vascular volume fraction	Vascular coverage fraction per high power field
Extravascular extracellular volume fraction	Glandular + stromal coverage fraction per high power field
Cell radius	Average cell radius in a high power field
Cellularity	Cell count per high power field

### Statistical considerations

#### Sample size calculation

A sample size of 280 subjects achieves 80 % power to detect a difference of 0.1 between two diagnostic tests whose specificities are 0.7 and 0.6. This calculation uses a two-sided McNemar test with a significance level of 0.05. The prevalence of patients with no cancer or insignificant cancer (≤Gleason 3 + 3) is estimated at 0.6. The proportion of discordant pairs is estimated at 0.2. Allowing for 10 % of patients being excluded from the reference standard, a total of 365 patients (50 to allow radiologist training, followed by 315 patients for the main study) will be recruited. Based on current practice at our institution, approximately 10 mp-MRI studies are performed per week in men that meet the eligibility criteria. With a 50 % recruitment rate (note our audit data from previous similar studies supports a recruitment rate of 90 %), complete recruitment is expected to take 73 weeks.

### Outcome measures

All primary and secondary outcomes are presented in Table 5 below.

**Table 5 Tab5:** Primary and secondary outcome measures

Primary outcome
Radiological assessment with added VERDICT MRI improves the diagnostic accuracy of mp-MRI for detection of significant prostate cancer by a minimum of 10 %
Secondary outcomes
• A group of diagnostic fluidic markers measured on the MesoScale discovery (MSD) platform and/or in DNA and RNA, can predict patients with a negative mp-MRI result (i.e. 1-2/5 Likert score).
• The use of patient serum-derived exosomes as ‘liquid biopsies’ for the identification of genomic and molecular aberrations that can be used to better predict patients with aggressive or high volume prostate cancer
• Technical validation of VERDICT:
○ VERDICT MRI is qualitatively and quantitatively repeatable
• Biological validation of VERDICT:
○ VERDICT cellularity measure correlates with histological cell density
○ VERDICT intracellular volume fraction correlates with segmented fractional histological intracellular component
○ VERDICT vascular volume fraction correlates with segmented fractional histological vascular component
○ VERDICT extracellular extravascular volume fraction correlates with fractional segmented histological glandular component + stromal component
• Set-up of imaging/fluidic marker outcome linked database

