## Methods and analysis

### Design

INNOVATE is a prospective cohort study with single centre recruitment. The primary objective is to assess whether supplementary VERDICT MRI improves the diagnostic accuracy of mp-MRI for detection of significant prostate cancer by a minimum of 10 %. The definitions of significant cancer have been provided previously [18].

Participants undergo standard mp-MRI [19] ± biopsy, together with studied index tests (fluidic markers and VERDICT MRI). A 50 patient pilot phase held over 1 year will provide histologically validated VERDICT MRI studies in order to familiarise radiologists and ascend the learning curve necessary for clinically interpreting VERDICT images. Initial evaluation of fluidic biomarker performance for prediction of a negative mp-MRI result will be conducted at the end of year 1 to derive thresholds for prospective application. An evaluation phase held over 2 years will prospectively test the added diagnostic accuracy of VERDICT to standard mp-MRI. During the evaluation phase, selected fluidic biomarker thresholds will be applied to collected samples to prospectively categorise patients into those expected to achieve negative and positive (with a lesion) mp-MRI scores.

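### The objective and primary outcome claim a gain of at least 10 %, but the study is sized to detect any difference from zero, so a significant result would not establish the 10 % minimum

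*Protocol article*

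**What the plan says.** Three parts of the protocol article bear on what the primary comparison is meant to show.

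- **Objective and outcome.** The Design section says: "The primary objective is to assess whether supplementary VERDICT MRI improves the diagnostic accuracy of mp-MRI", and sets the required improvement at 10 % or more. Table 5 (Outcome measures) repeats this as the only primary outcome: adding VERDICT "improves the diagnostic accuracy of mp-MRI for detection of significant prostate cancer by a minimum of" a stated figure, which is 10 %.
- **Sample size calculation.** The 280 subjects are given as the number with 80 % power "to detect a difference of 0.1 between two diagnostic tests whose specificities are 0.7 and 0.6". The method behind that figure is then named: "This calculation uses a two-sided McNemar test with a significance level of 0.05". The share without significant cancer is put at 0.6 and the proportion of discordant pairs at 0.2.
- **Data analysis, VERDICT MRI.** Specificity with and without VERDICT is compared at a Likert threshold of 3, to see whether VERDICT adds anything diagnostically. This section gives no 10 % threshold and names no test.

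**The concern.** As worded, the objective and outcome make 10 % a floor that the improvement must reach. In the sample size calculation, 0.1 is the size of effect assumed to be true, and the value being tested is zero. These are different hypotheses. Rejecting a null of equal specificities shows that the difference is not zero; it does not show that it is 10 points or more.

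The wording of the trial's main conclusion is at stake. A significant McNemar result could be read as meeting the primary outcome in Table 5 when the data remain compatible with a much smaller gain. A reader could also take the stated 80 % as the chance of demonstrating a 10 % improvement, which it is not.

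**Working it through.** **Inputs** (all from Sample size calculation): 280 evaluable subjects; share without significant cancer 0.6; specificities 0.7 and 0.6, so d = 0.10; discordant proportion ψ = 0.2; two-sided α = 0.05. One pair per patient is assumed, as that section does.

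**1. Reproduce the plan's figure.**
- Men contributing to specificity: n = 280 × 0.6 = 168.
- Discordant cells: (0.2 + 0.1)/2 = 0.15 and (0.2 − 0.1)/2 = 0.05, so the favourable share is 0.15/0.2 = 0.75.
- Exact two-sided McNemar test, with the number of discordant pairs distributed Bin(168, 0.2): power is 0.8006 at n = 168 and 0.7977 at n = 167.

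The stated 280 and 80 % are therefore right, as power against a difference of zero.

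**2. What observed gain is significant?** The expected number of discordant pairs is 168 × 0.2 = 33.6.
- Exact test, 33 discordant pairs: a split of 23 to 10 is needed, a gain of 13/168 = 7.7 points.
- Exact test, 34 discordant pairs: a split of 24 to 10 is needed, a gain of 14/168 = 8.3 points.
- Uncorrected normal approximation: 1.96 × √(0.2/168) = 6.8 points.

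All are below 10.

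**3. How often does a smaller true gain give significance?** At d = 0.05 with ψ = 0.2 and n = 168, power is 24 % with the exact test (31 % uncorrected).

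**4. What does an observed gain of exactly 10 points support?** SE = √((0.2 − 0.01)/168) = 0.0336. The 95 % interval is 0.10 ± 1.96 × 0.0336, or 3.4 to 16.6 points.

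**5. Chance of meeting the outcome as worded when the true gain is exactly 10 points.**
- Point estimate at or above 10: about 52 % by simulation.
- Lower 95 % limit above 10: Φ(0 − 1.96) = 2.5 % (2.3 % by simulation), whatever the sample size.

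**6. True gain needed to exclude gains of 10 points or less.** Power = Φ((d − 0.10)/SE − 1.96), with SE = √((ψ − d²)/168) and the protocol's ψ = 0.2.

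| True gain | SE | Power |
|---|---|---|
| 15 points | 0.0325 | 34 % |
| 18 points | 0.0316 | 72 % |
| 19 points | 0.0312 | 82 % |
| 20 points | 0.0309 | 90 % |

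About 80 % power needs a true gain of about 19 points. Higher discordance would be an assumption outside the protocol and would raise this figure: at 20 points, power is 81 % with ψ = 0.25 and 72 % with ψ = 0.30.

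**The case against.** The strongest reply is that nothing in the design is miscalculated and that the 10 % minimum is loose wording for the smallest difference the study is sized to detect. The analysis section supports this, because it asks only whether VERDICT adds anything, which is the zero-difference question. That reading is plausible. However, neither the Design section nor Table 5 says so, and those are the two places that define the objective and the primary outcome. If the wording is only loose, correcting it costs nothing in conduct.

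Three stronger readings are tempting, and the documents do not support them.

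- *The trial has only 2.5 % power.* That figure is the rejection rate at the boundary of a margin test that the protocol never proposes. It is the same at any sample size, so it is no measure of weakness in this trial. It shows only that a planning difference cannot also serve as the minimum to be demonstrated.
- *The investigators will report significance as meeting the 10 % minimum.* The article does not say that significance alone counts as success. McNemar is named only for the sample size, and a detailed success rule may sit in the full protocol or analysis plan.
- *The 10 % is unresolved between absolute and relative.* The objective and Table 5 do not say which, but 0.7 against 0.6 in the sample size section fixes it as 10 absolute points of specificity.

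**Conclusion.** The point stands as a mismatch between the claim and the hypothesis tested. The 80 % power applies to detecting a non-zero difference when the true difference is 0.1, and not to showing a gain of at least 10 points. A significant result could follow from an observed gain of about 8 points, or in about a quarter of trials from a true gain of 5 points. It would not by itself justify the wording of Table 5.

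These figures rest on 168 men without significant cancer, discordance of 0.2 and one pair per patient. The mismatch itself does not depend on those values. It is a correction of wording and of the permitted claim, and should be made before results are reported because it concerns the primary outcome. It is not a finding that the sample size is wrong or too small.

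**What to change.** Reword the primary objective and Table 5 along these lines: *mp-MRI plus VERDICT has higher specificity than mp-MRI alone at Likert 3 or above (H0: difference = 0); 10 absolute percentage points is the planning difference.* Report the paired difference in specificity with its 95 % confidence interval. Claim a gain of at least 10 points only if the lower limit is at or above 10.

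The cost is a few sentences and a less strong headline claim. Sample size, test and conduct are unchanged. If a 10-point minimum is truly meant, it needs a stated margin and a larger assumed true gain; adding patients while still assuming a true gain of 10 points would not help.

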### Data analysis and outcome assessment

#### Fluidic markers

The diagnostic accuracy of fluidic markers will also be evaluated against the Likert score from the mpMRI, to gauge whether they may be used as a sensitive gatekeeper to reliably exclude patients in whom the mpMRI result is likely to be negative (Likert 1/2). To do this, results of each fluidic marker will be compared against the Likert score and a sensitivity and specificity will be acquired allowing for Receiver operating curve (ROC) and area under curve (AUC) analysis to subsequently be performed. Cancer volume and Gleason grade will be correlated with exosome levels, to judge whether they may have any useful clinical application as biomarkers in the future.

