#### Fluidic markers from blood and urine

Whole blood, serum, plasma and urine will be collected from all patients in the study using existing standard operating procedures (SOPs) and assayed for diagnostic markers (PCA3, AGR2 (Anterior gradient protein 2 homolog), SPON2 (spondin 2), TMPRSS2 (Transmembrane protease serine 2), EN2(Homeobox protein engrailed-2), MSMB(Beta-microseminoprotein), GDF15(Growth differentiation factor 15), SIK2 (Serine/threonine-protein kinase) and CD10(cluster of differentiation 10)). Protein markers in all matrices will be assayed on a MesoScale discovery (MSD) platform and deoxyribonucleic acid (DNA) will be extracted from whole blood to investigate 22 prognostic single nucleotide polymorphisms (SNPs) associated with aggressive disease. RNA for the PCA3 and TMPRSS2 quantification from urine will be extracted according to an SOP already developed in our laboratory. qPCR for PCA3, TMPRSS2, 3 control genes (TBP (TATA binding protein), SDH (succinate dehydrogenase), RPLP2 (60S acidic ribosomal protein P)) and PSA will be used in triplicate to quantify gene expression. During the pilot phase we will continue to horizon scan for new markers and have included scope to add 2 further markers as evidence comes to light and assays are developed e.g. GOLM1 (golgi membrane protein 1), NAALADL2 (N-Acetylated Alpha-Linked Acidic Dipeptidase-Like 2).

We will also extract exosomes from the serum and plasma (when possible) of patients to derive molecular tumour characteristics using fluorescence-lifetime imaging microscopy (FLIM) based measurements as well as analysis of exosomal micro RNA (miRNA) that are known to be associated with cell-to-cell communication and the development of cancer as well as immunosuppression leading to the development of further pre-metastatic niche. Functional blood-derived miRNAs have been recognised as potential robust biomarkers in the detection of various types of cancer. The ability to screen for these miRNAs and to perform FLIM of the epidermal growth factor receptor (ErbB) family members will add important prognostic and predictive information for diagnosis and stratification of patients to treatment. Finally, we will separate peripheral blood mononuclear cells (PBMCs) from whole blood of newly diagnosed prostate cancer patients to perform immunophenotyping of immune cell populations with an ultimate goal to provide multi-modality patient stratification.

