### VERDICT MRI: histology/mpMRI based reference standard

A lesion based reference standard will be derived (Fig. 3). mp-MRI has a 90-95 % negative predictive value for exclusion of aggressive disease [22] and will therefore form the reference for the index tests when mp-MRI is negative (Likert score 1-2/5). The positive predictive value of mp-MRI is limited and reported between 60-70 %. Therefore, where mp-MRI is positive (Likert score 3-5/5) a prostatectomy or biopsy will be performed if clinically appropriate. The prostatectomy or biopsy will then supersede the mp-MRI as the reference standard. Where a biopsy or prostatectomy is not performed, patients will be followed up with interval (6 months-1 year) mp-MRI as part of standard clinical care. A progressive Likert score (3/5 - > 4/5 or 5/5) or a progressive lesion (previously scored 4-5) on repeat mp-MRI will be considered as positive for the reference standard. A negative Likert score (1-2/5) on the repeat mp-MRI will be considered as negative for the reference standard. Lesions that remain stable with Likert score 3/5 will be deemed indeterminate and excluded from analysis unless biopsied. Based on previous internal audit, the total number of excluded patients is predicted to be approximately 10 %.

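### The exosome secondary outcome is better prediction of aggressive or high-volume cancer, but the only stated analysis is a correlation with grade and volume that leaves predictive performance undetermined

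*Protocol article*

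**What the plan says.** Under Outcome measures, Table 5 lists a liquid-biopsy use of serum exosomes among the secondary outcomes. Its aim is given as "identification of genomic and molecular aberrations that can be used to better predict patients with aggressive or high volume prostate cancer".

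Under Fluidic markers from blood and urine, the exosome measurements are FLIM-based molecular characteristics and exosomal miRNA. Extraction is from serum and plasma, with the qualifier that it is done when possible.

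Under Data analysis and outcome assessment, Fluidic markers, the exosome analysis is one sentence. Its method is: "Cancer volume and Gleason grade will be correlated with exosome levels". The declared purpose of doing so is "to judge whether they may have any useful clinical application as biomarkers in the future". The same paragraph gives a discrimination analysis for fluidic markers generally, but against a different target: "results of each fluidic marker will be compared against the Likert score and a sensitivity and specificity will be acquired", leading to ROC and AUC.

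Under Histopathological data processing and collection, Gleason score and tumour volume or core length are read from biopsy and whole-block sections. On who provides tissue, the reference-standard section says "where mp-MRI is positive (Likert score 3-5/5) a prostatectomy or biopsy will be performed if clinically appropriate". The Discussion adds that sampling men without evident tumour would be unethical at this stage.

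**The concern.** The outcome and its analysis ask different questions. The outcome is about telling which patients belong to a class (aggressive or high-volume cancer), and doing so better than something else. The analysis is an association between a marker level and two histological measurements. No sensitivity, specificity or AUC against aggressive cancer is stated for exosomes, and no benchmark is named for the word better.

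The men missing from the correlation matter most. A man with a negative mp-MRI generally has no study tissue, and a benign biopsy has no Gleason grade. These men make up much of the group from which a predictor must separate aggressive disease. If the exosome result is later reported against Table 5, a correlation among men with cancer could be read as evidence of prediction in men under suspicion, which it does not supply.

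**Working it through.** **Plan's own figure.** None is given for the exosome outcome. The stated sample size belongs to the primary specificity comparison. It reproduces with an exact two-sided McNemar test (168 reference-negative men, 168 / 0.6 = 280, power 0.8006) and does not bear on this point.

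**Texts side by side.**

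| | Outcome (Table 5) | Exosome analysis (Fluidic markers) |
|---|---|---|
| Variable | Genomic and molecular aberrations | Exosome levels |
| Target | Patients with aggressive or high-volume cancer | Gleason grade and cancer volume |
| Measure | Better prediction | Correlation |
| Benchmark | Implied, not named | None |

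The ROC analysis in the same paragraph does not fill the gap, because its target is the mp-MRI Likert score.

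**How many men have no study tissue.** From Sample size calculation: 40 % significant cancer (1 − 0.6), and specificity 0.6, taken here as mp-MRI alone. Sensitivity is not given, so 0.90 to 1.0 is assumed.

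- Share mp-MRI positive = 0.4 × Se + 0.6 × (1 − 0.6) = 0.4 × Se + 0.24.
- Share negative = 0.36 (Se = 1.0) to 0.40 (Se = 0.90).
- Of 315 main-study men: 113 to 126. Men with benign biopsies come on top.

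**Does the correlation among cancers fix the AUC in all men?** Simulation of 400,000 men with 40 % significant cancer. Assumed, because the documents do not give them: 10, 20 or 30 % insignificant cancer, a normal severity scale on which the upper part is significant, marker = 0.4 × severity + √(1 − 0.4²) × noise, and a marker mean in men without cancer shifted by +0.8, 0 or −0.8 SD.

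- Spearman correlation among men with cancer: about 0.38 throughout.
- AUC for significant cancer within men with cancer: 0.68 to 0.70.
- AUC for significant cancer across all men:

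| Insignificant cancer | Shift +0.8 | Shift 0 | Shift −0.8 |
|---|---|---|---|
| 10 % | 0.381 | 0.565 | 0.741 |
| 20 % | 0.452 | 0.605 | 0.740 |
| 30 % | 0.517 | 0.631 | 0.733 |

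The same correlation is compatible with an AUC anywhere from 0.38 to 0.74.

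**With zero correlation among cancers.** Let the marker be flat across all cancers and 1 SD lower in men without cancer, with s the share of insignificant cancer. Then AUC = [s × 0.5 + (0.6 − s) × Φ(1/√2)] / 0.6, with Φ(1/√2) = 0.760.

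- s = 0.1: (0.050 + 0.380) / 0.6 = 0.72
- s = 0.2: (0.100 + 0.304) / 0.6 = 0.67
- s = 0.3: (0.150 + 0.228) / 0.6 = 0.63

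The simulation gave 0.718, 0.674 and 0.630.

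**Would a useful marker be dismissed?** Take a marker 1 SD higher in significant cancer and otherwise flat. Its AUC for significant cancer versus all other men is Φ(1/√2) = 0.76. Its rank correlation with grade is 0.00 if only significant cancers are used, but 0.36 once 3+3 cancers (assumed 20 % of men) are included. With 0.40 × 315 = 126 and 0.20 × 315 = 63 men, n = 189. The Fisher interval is tanh(atanh 0.36 ± 1.96/√186) = 0.23 to 0.48. The stated correlation would detect this marker.

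**The case against.** The strongest reply is that this is discovery work and is labelled as such. The analysis sentence claims only to judge possible future usefulness, grade and volume are the natural counterparts of aggressive and high-volume, and correlating a candidate marker with them is a usual first step. This stands, and it limits the weight of the point. It does not remove the mismatch, because Table 5 still words the outcome as better prediction of a class of patients.

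A second reply is that nothing in the analysis sentence restricts it to men with cancer. Volume could be set to zero and benign histology made the lowest category. Some mp-MRI-negative men may also have earlier histology, since men biopsied elsewhere more than six months before are eligible. The restriction is indeed inferred from where grade, volume and tissue come from, which is why the claim is that the correlation is largely, not wholly, confined to men with cancer. The article states no such coding.

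A third reply is that exosome levels may be shorthand for the miRNA and FLIM readouts. In a condensed article that is plausible, so the difference between levels and aberrations carries little weight alone.

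A reader might go further and infer that the analysis cannot show prediction at all, or that a good marker would be reported as useless. The documents do not support either. If the outcome is read as grading known cancers, a correlation is weak but real evidence. The 0.00 correlation arises only by leaving out 3+3 cancers, which the article does not do.

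**Conclusion.** The point holds in a limited form. A stated secondary outcome (better prediction of aggressive or high-volume cancer) is paired with a stated analysis that does not measure it. This is a conflict between two things the article fixes, not a detail left to an analysis plan. The correlation says something about aggressive versus indolent disease among proven cancers. It leaves discrimination among all enrolled men undetermined in either direction and says nothing about gain over PSA.

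The AUC ranges are illustrations. They rest on the plan's 40 % significant cancer, on assumed shares of insignificant cancer, on assumed marker distributions in men without cancer, and on every man having a result. They show that the correlation does not settle the question; they do not forecast exosome performance. Severity is modest: the outcome is secondary, its analysis is exploratory, and the primary comparison and its sample size are unaffected.

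**What to change.** Either of two changes resolves it.

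1. In Data analysis and outcome assessment, Fluidic markers, add for the exosomal miRNA and FLIM readouts a patient-level AUC, with sensitivity and specificity, for aggressive or high-volume cancer versus not. Include all men with both an exosome result and a reference classification. The reference standard is lesion-based, so state how it is reduced to one result per man, for example positive if any lesion is positive. Report the gain over PSA, the benchmark the Abstract itself uses for novel blood and urine tests. Keep the correlation with grade and volume as a descriptive analysis in men with cancer.
2. Otherwise, reword the Table 5 outcome as an exploratory association between exosome measurements and grade and volume in men with histologically proven cancer.

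The second change costs only wording. The first uses samples and reference results already planned, provided exosome readouts are available beyond the men with cancer and a PSA value is on record. It has two drawbacks: mp-MRI-negative men would be classed as negative by imaging alone, and because extraction is qualified as when possible, some men may have no exosome result. The number analysed, and the reasons for missing results, should be reported.
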